# Where is an emotion? Using targeted visceroception as a method of improving emotion regulation in healthy participants to inform suicide prevention initiatives: a randomised controlled trial

**DOI:** 10.1186/s13063-020-04479-9

**Published:** 2020-07-14

**Keywords:** Emotion regulation, Suicide, Localisation, Interoception, Visceroception

## Abstract

**Background:**

William James’ 1884 paper “What is an emotion?” has generated much recent interest in affective science regarding somatic contributions to emotion. Studies of interoception (“sensing the physiological condition of the body”) suggest that sensing specific parts of the body contributes to the production of emotion, namely when sensing the viscera (i.e. “visceroception” of the heart, gut or lungs). Improved visceroception has, for instance, been linked to increased emotional intensity, suggesting a role for interoception in emotion regulation that may pertain specifically to visceral bodily locations. Thus, in addition to asking James’ question, “*What* is an emotion?”, we ask, “*Where* is an emotion?”. Further, there is an evidence base pointing to the connections between emotion regulation and suicide, and between interoception and suicide. This is a preliminary trial investigating whether targeted interoception/visceroception improves emotion regulation. Ultimately, the overall project aims to inform suicide prevention efforts.

**Methods:**

The trial utilises a pre-test/post-test control group design, with two experimental groups undergoing visceroceptive interventions (focussing on areas pertaining to the gut or heart) and a control group. The interventions will run for 8 weeks. A spatial cueing task will measure reaction times to bodily changes relating to lower abdomen or chest focus. A stop/signal task will measure emotional inhibition, which is hypothesised to obscure awareness of active bodily locations. Visceroceptive ability will be tracked using a heartbeat estimation task, a water load test, and by self-report questionnaire. The sample will consist of healthcare professionals and healthcare students. Despite these being groups that represent a relatively high suicide risk among professional and student groups, all participants will be healthy, given the preliminary nature of this trial.

**Discussion:**

To our knowledge, this will be the first project to address whether emotional feeling presents as a localised bodily phenomenon and whether trained awareness of emotional localisation can improve emotion regulation. It will also be the first to investigate relationships between interoception and emotional inhibition (i.e. whether a sustained interoceptive practice leads to the disinhibition of bodily emotional sensations, which can positively contribute to emotion regulation). These empirical findings on emotion regulation from a healthy sample will be used to inform a desk-based enquiry into the role of embodied emotion in suicide prevention, which may make a significant contribution to a growing evidence base on interoception and suicide.

**Trial registration:**

ACTRN12619000324112. Registered on 4 March 2019. Universal Trial Number (UTN): U1111-1221-0201.

## Background

According to William James in the 1884 paper “What is an emotion?” [1], emotion is defined by, or to a great extent involves, the perception of our body. Some recent developments in affective science take their lead from James [2, 3] in involving a form of body focus named “interoception” (the “sense of the physiological condition of the body” [4]).

There are a number of distinctions to be made to fully define interoception. Firstly, it is distinct from exteroception (i.e. sensing the external environment). Interoception is further differentiated into visceroception (i.e. sensing the viscera) and proprioception (i.e. sensing the skeletal muscles and position of the body). Visceroception is, in turn, to be differentiated into cardioception (i.e. interoception of the heart) and gastroception (i.e. interoception of the gut). There are three dimensions of interoception: sensitivity (i.e. the objective detection of bodily activity), sensibility (i.e. the subjective experience of bodily activity), and metacognitive awareness (i.e. the extent to which sensitivity correlates with sensibility). Much of the emotion research involving interoception has focused on interoceptive—specifically visceroceptive—sensitivity as a measure of interoceptive accuracy, such as in relation to heart beat. Finally, superior visceroception—such as greater accuracy in heart rate detection—has been linked to greater emotional intensity [5], and such improvements in accuracy can be trained [6, 7].

The importance of emotional feeling for well-being has previously been emphasised, with indications that avoidance of negative feeling is linked to psychological disorders [8] and emotion dysregulation [9–11]. Ineffective emotion regulation has in turn been correlated with suicide ideation (i.e. having suicidal thoughts), the desire to attempt suicide [12], and actual suicide attempts [13]. In the specific case of interoception—as one aspect of emotional feeling—low levels have been linked to an increased likelihood of harming oneself [14].

Few studies, however, have addressed this connection between interoception and self-harm or suicide, and those that have were limited to interoceptive sensibility. For instance, Forrest et al. [15] found negative correlations between suicidality and interoceptive sensibility. Forcano et al. [16] reported that women with bulimia nervosa who had attempted suicide had yet greater interoceptive sensibility deficits than those who had not attempted. A more recent study [17] reported that people with lifetime suicide attempts tend to distract themselves from bodily sensations, and those with lifetime suicide ideation reported increased worry about bodily sensations. There was a lack of trust of bodily sensations for participants across the suicidal continuum. Overall, suicidal individuals reported lower levels of interoceptive sensibility than non-suicidal individuals, and this effect was more pronounced at the more extreme (more suicidal) end of the continuum. These authors conclude that “a tendency to ignore or distract oneself from sensations of pain or discomfort may be particularly relevant to the capability for suicide” (p. 7).

To date, no study has investigated whether differential improvements in emotion regulation are possible from practice in the differing forms of visceroception, including cardioception and gastroception. Relatedly, no study has considered whether the embodied aspects that play a part in emotion regulation can be localised in an area of the body corresponding to a form of visceroception, i.e. to cluster in the chest (accessed by cardioception) or the abdomen (accessed by gastroception). This may be especially applicable to the early onset of an emotional response, prior to the development of a “multi-componential syndrome” (see [18]) where body and mind become activated at many locations (e.g. fast heart, clammy palms, increased body temperature, “butterflies” in the stomach), over potentially much longer timescales, and which includes cognitive appraisals of the stimulus. It may be that, during the moments following the presentation of an emotional stimulus or trigger, it is vital to engage in visceroception—as a form of “sensory monitoring” (i.e. the improved “ability to access, accurately identify, regulate, and act on information conveyed in one’s feelings” [19], p. 392) before the emergence of multi-componential syndromes, which may include problematic “emotional cascades” whereby increasingly distressing vicious cycles are generated [20]. If, then, there is a connection between visceroception, improved emotion regulation, and the prevention of cascades, this may be due to improved sensory monitoring of early stage emotional activation in a localised area—a cardioceptive or gastroceptive cluster. Indeed, the gut in particular has been the focus of much emotion research, such as the discovery of the enteric nervous system and gut-brain-emotion interactions [21] including the established gut-emotion connections via the vagus nerve [22].

Finally, there are grounds for thinking that the current lack of evidence regarding localisation may be due to habitual attentional processes. Selective attention involves the concurrent activation of attention to a stimulus and deactivation of attention to a non-stimulus, i.e. attentional inhibition. Decreased interoception may result in inhibited awareness of the physiological condition of the body. This inhibition may ultimately result from the functional dominance of exteroception over interoception during early infancy, i.e. awareness of events in the external world likely has greater survival/social value than the awareness of inner processes; hence, finite attentional resources are allocated accordingly and reinforced over time [23]. Normal development then results in a ubiquitous trade-off between (i) having improved outwardly focused interpersonal/social functioning and (ii) improved personal connection with embodied emotion. With a tendency to orient externally, we may only become aware that our body is active at a later stage of a longer duration multi-componential syndrome and be unable (without training) to attend to an early, brief, principle location of emotional experience. Improvements in interoception over an extended time period may enable identification of location, possibly through a gradual process of disinhibition.

The potential benefit of disinhibition, as opposed to avoidance/inhibition, is the focus of this project, and in particular that a key element may be missing in our current understanding of emotion that is fundamental for emotional feeling: the identification and connection with localised emotion, with a focus on the chest and lower abdomen areas of the body.

### Aims of the project

The overarching aim is to advance understanding of the localisation of emotion via interoceptive training and how this may relate to emotion regulation, with a view to laying the groundwork for the development of clinical interventions pertaining to suicidality.

### Research questions

(RQ1) Is emotional/affective feeling localised?

(RQ2) Can targeted interoception result in indications of localised emotion?

(RQ3) Is the *unlocalisability* of emotional feeling due to inhibition?

(RQ4) What implications does access to localised emotion have for emotion regulation in its relationship with suicide prevention?

## Methods and design

### Design

The project will be a parallel group trial using a pre-test/post-test control group design (Fig. 1). There will be two data points (baseline and follow-up) with comparisons between two experimental groups (gastroception vs. cardioception; focussing on the inside of the lower abdomen or chest area, respectively) and a control group.

**Fig. 1 Fig1:**
[figure not shown]
Trial overview

Since emotion research deals with constructs that are multiply realised [24], the project will employ multiple measures. There will be two primary, single-blinded studies, both laboratory-based, one utilising a spatial cueing task and another utilising a stop/signal task. In addition, physiological and self-report measurements will be taken (these are described in detail below).

### Study population

The sample for the main data collection will be drawn from across the health professions and student healthcare cohorts in the Wellington area, New Zealand. Given the preliminary nature of the trial, only healthy individuals will be recruited at this stage (with health status established by self-report; see below).

Medical students evidently experience difficulties in emotion regulation when dealing with the many stressful situations faced during training [25]. Further, a high prevalence of suicide ideation has been found in medical student populations (e.g. 11% incidence [26]; 15% incidence [27]). Qualified doctors also experience emotion regulation difficulties [28, 29], with male doctors having a suicide rate that is 1.4 times higher than in the general male population, and 2.3 times higher among female doctors than in the general female population [30].

Nurses may also be at greater risk of suicidality, with recent UK statistics [31] indicating this group to be the most at-risk of all health professions [32]. Nursing students may, too, face similar challenges to their medical counterparts.

Finally, allied health professionals—particularly female—have also been identified as at risk [33] and hence will be included in the sample, along with allied health students given that these, too, may have similar experiences to their medical and nursing counterparts.

### Sample size

A power analysis calculation was based on reaction time (RT) measures in Silverstein et al. [34], who reported a mean RT of 2134.1 ms (SD = 856.6 ms) pre-treatment and 1403.6 ms (SD = 462.3 ms) post-treatment for meditators, and 1865.1 ms (SD = 800.4 ms) pre-treatment and 1893 ms (SD = 780.6 ms) post-treatment for controls. This gave a treatment-by-time partial eta-squared of 0.15, with a *p* value of 0.03. Using the same partial eta-squared for the three group, two time point studies, with alpha = 0.05 and 80% power, a minimum of 54 participants would be required in total (across all group conditions). This equates to a minimum of 18 participants per group to detect the main effect in the spatial cueing task. (regarding the stop/signal task, Verbruggen and De Houwer [35] detected effects in a single group with a sample size of 23 participants.) We will aim for 70 participants in total, assuming a drop-out buffer of approximately 5–10 participants. This will allow 20+ participants in each group.

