### Randomisation

Each participant will be assigned a number ID in order of recruitment into the study. Once the required sample size has been reached and scheduling completed for laboratory attendance, these numbers will be entered into an online random number generator (http://www.randomization.com/) to allocate these numbers into one of the three blocks (cardioception group; gastroception group; control group). The allocation ratio for the groups will be 1:1:1.

Other randomisation pertains to counterbalancing over trials and blocks of trials. This will be undertaken to control for ordering effects and will be achieved using the standard functions of the stimulus presentation software programme *SuperLab (Version 6, Cedrus)*.

Participants will be told of their allocation immediately after the completion of baseline data collection. Concealment will be ensured using sealed notes provided during this first laboratory visit, within the process described below (see the “Confidentiality and single blinding” section).

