### Spatial cueing task

One of the interoception groups will show significantly faster reaction times (RTs) and greater response frequency to emotional stimuli regardless of cue type compared with each of the other groups after baseline; plus, there will be a greater change between baseline and follow-up. Each of the interoception groups separately and combined will show significant differences from the control group.One set of cues for the same group (i.e. the interoception group in (1)) will facilitate significantly faster RTs and greater response frequency. This set will match the target area of the body for that group (i.e. a chest cue for the cardioception group; a lower abdomen cue for the gastroception group). The “matching” cue for the other interoception group will not facilitate faster RTs or greater response frequency. If any cue facilitates faster RTs or greater response frequency for the other groups, it will be the same cue that facilitates for the interoception group in (1).This same group will display greater within-group coherence in the location of the body indicated to be active during trials compared with the other groups after baseline. It will also show the greatest change between baseline and follow-up compared with the other groups.This same group will report greater intensity compared with the other groups after baseline. It will also show the greatest change between baseline and follow-up compared with the other groups. The interoception groups combined will report greater intensity than the control group.This same group will show greater heart rate deceleration after baseline following the presentation of emotional stimuli compared with the other groups; both interoceptive groups will show greater heart rate deceleration than the control group.

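### The effect behind the stated 80% power includes an unremarked 269 ms pre-treatment gap in the cited study; if that gap arose by chance, unadjusted group-by-time power at 54 is about 46-50%

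*Protocol article*

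**What the plan says.** The Sample size section bases the calculation on one cited study with two groups. The treated group's line reads "mean RT of 2134.1 ms (SD = 856.6 ms) pre-treatment and 1403.6 ms (SD = 462.3 ms) post-treatment for meditators". Next to it the section gives the comparison group's figures: "1865.1 ms (SD = 800.4 ms) pre-treatment and 1893 ms (SD = 780.6 ms) post-treatment for controls". The effect size drawn from these is stated as follows: "This gave a treatment-by-time partial eta-squared of 0.15, with a *p* value of 0.03". That value is then carried over to this trial: "Using the same partial eta-squared for the three group, two time point studies". The resulting requirement is given in these words: "with alpha = 0.05 and 80% power, a minimum of 54 participants would be required in total". The section sets a target of 70 with 5-10 expected to drop out, so about 60-65 completers.

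The Randomisation section states: "The allocation ratio for the groups will be 1:1:1". Participants learn their allocation only after baseline measurement.

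The Data analysis section plans GEE on the two data points with interactions. It names no baseline reaction-time covariate and does not rule one out.

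**The concern.** A treatment-by-time contrast is the difference between two changes, so it contains whatever gap the groups had at the start. In the cited study the group that improved was also the group that started slower, and this enlarges the contrast. The protocol does not remark on it.

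In a randomised trial the expected baseline difference is zero, so the expected group-by-time contrast equals the expected follow-up difference. A planning effect that owes about a third of its size to a starting gap carries over in full only if that gap would have persisted without treatment.

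This is the protocol's only formal power calculation. If the effect is too large for a randomised setting, a null group-by-time result would be read against a stated 80% when the test may have had about an even chance of missing an effect as good as the cited study's.

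**Working it through.** **Inputs (Sample size section).** Meditators 2134.1 (SD 856.6) to 1403.6 (SD 462.3) ms; controls 1865.1 (SD 800.4) to 1893 (SD 780.6) ms; partial eta-squared 0.15; p = 0.03; alpha 0.05; three groups, two time points; N = 54. The cited study's group sizes, allocation method and pre-post correlation are not given.

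**1. The plan's own figure.** f² = 0.15/0.85 = 0.1765. The test has 2 numerator df and noncentrality N × f².
- Large-sample chi-square (the Wald form used with GEE): power at 54 is 79.5%, and 80% is reached at N = 55. The stated 54 is reproduced.
- Exact F with N − 3 error df: power at 54 is 77.0%, and 80% is reached at N = 58.

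**2. The contrast.**
- Changes: 2134.1 − 1403.6 = 730.5 ms faster (meditators); 1893 − 1865.1 = 27.9 ms slower (controls).
- Contrast: 730.5 + 27.9 = 758.4 ms.
- Gap before treatment: 2134.1 − 1865.1 = 269.0 ms.
- Gap after treatment: 1893 − 1403.6 = 489.4 ms.
- Share of the contrast due to the starting gap: 269.0/758.4 = 35.5%.

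**3. Implied pre-post correlation.** Assume about 31 subjects split equally.
- F = 0.1765 × df with p = 0.03 gives about 29 error df. Then t = √(0.1765 × 29) = 2.26.
- SD of change = (758.4/2.26)/√(2/15.5), about 933 ms.
- Pooled variances: pre (856.6² + 800.4²)/2 = 687,202; post (462.3² + 780.6²)/2 = 411,529.
- Covariance = (687,202 + 411,529 − 933²)/2, about 114,000.
- Mean SD product: (856.6 × 462.3 + 800.4 × 780.6)/2 = 510,399, so r is about 0.22. The slope of post on pre is b = 114,000/687,202, about 0.17.
- Splits of 40:60 to 60:40 give r of about 0.22-0.28 and b of about 0.17-0.22.

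**4. Effect if the gap was chance.** Adjusted effect = 489.4 + b × 269.0, about 534-548 ms. The 758.4 ms exceeds this by 38-42%. Scaled f² = 0.1765 × (adjusted/758.4)² = 0.087-0.092, a partial eta-squared of about 0.080-0.085.

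Unadjusted group-by-time power is then 46-48% (F) or 48-50% (chi-square) at 54, and 50-58% at 60-65 completers.

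**5. Sensitivity to how much of the gap persists** (b = 0: none; b = 1: all):

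| b | Effect (ms) | Contrast too large by | Power at 54, F / chi-square | Power at 60, F / chi-square |
|---|---|---|---|---|
| 0 | 489 | 55% | 39% / 41% | 43% / 45% |
| 0.2 | 543 | 40% | 47% / 49% | 52% / 54% |
| 0.5 | 624 | 22% | 59% / 62% | 64% / 67% |
| 0.75 | 691 | 10% | 69% / 71% | 74% / 76% |
| 1 | 758 | 0% | 77% / 80% | 82% / 84% |

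**6. Is chance plausible?** With about 31 subjects split equally, t for the baseline gap = 269/(829 × √(2/15.5)) = 0.90, p about 0.37. Chance is compatible with the figures, but this does not show that it was chance.

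**7. Baseline-adjusted test on the same inputs.** Residual SD = √(411,529 − 0.166 × 114,000), about 627 ms. Effect = 534/627 = 0.85 SD, f² = 0.85²/4, about 0.18, and power at 54 is about 78% with equal groups. Over 24-38 subjects and 33-67% meditators in the cited study, it is about 76-88%.

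**The case against.** The strongest reply is that a treatment-by-time contrast is meant to remove a stable pre-existing difference. It overstates benefit only to the extent that the gap was chance and would have regressed. The protocol does not say how the cited study formed its groups, and the fact that this trial randomises does not explain why those groups differed. If the meditators were a stably slower group, 758.4 ms stands and power stays at 77-80%. This objection stands, and it is why the finding is conditional.

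Two further points stand in part. The shortfall belongs to an unadjusted test; the Data analysis section reads most naturally that way, but it is a summary, and an analysis plan not shown here could adjust for baseline. Also, 54 is a minimum: the planned 60-65 completers raise the conditional figure, though only to 50-58%.

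Three stronger readings are tempting but unsupported:
- *That the true power is 46-50%.* This is one scenario, resting on a chance gap, an assumed size and split of the cited study, and a back-derived correlation.
- *That the protocol miscalculated.* It did not: 54 follows from 0.15 by the large-sample test. The issue is the choice of planning input.
- *That hypothesis 1 tests something other than what was powered.* It opens with group differences at follow-up, but the sentence runs "regardless of cue type compared with each of the other groups after baseline; plus, there will be a greater change between baseline and follow-up", so the change comparison is there too.

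**Conclusion.** The point holds in conditional form. It is certain from the printed means that 269.0 of the 758.4 ms (35%) behind the planning effect is a pre-treatment gap, that it lies in the inflating direction, that this randomised trial does not expect one, and that the protocol does not mention it.

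The cost in power depends on how far the cited gap would have persisted, which cannot be settled from the protocol. Power at 54 for the unadjusted test runs from about 39% to 80%, and is about 46-50% if the gap was chance. Only full persistence preserves the stated figure. These numbers assume about 29 error df in the cited study, splits of 40:60 to 60:40 for the chance case, and the same carry-over of the effect to three groups that the plan makes.

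An unqualified 80% is therefore not well supported. The trial has not been shown to be underpowered.

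**What to change.** In the Sample size paragraph, state that the cited groups differed by 269 ms before treatment. Replace the unqualified 80% with power conditional on that gap: for the unadjusted group-by-time test, about 46-50% at 54 and 50-58% at 60-65 completers if it was chance, 77-80% at 54 if it was fully stable, and about 39-80% at 54 overall. If the authors know how the cited groups were formed, they should say so and justify the value used.

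Alternatively, make the primary reaction-time comparison baseline-adjusted, using the baseline measurement already collected, and quote power for that test: about 76-88% at 54 on the same inputs, 78% with equal groups.

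Either change costs one paragraph, and the second also a sentence in Data analysis. No extra recruitment or procedure is needed. The downside is a less favourable or more qualified power statement.
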